#### Statistical assessment

2.8.19

We defined two primary outcomes for the study to capture both changes in glucose control and the change of glucose control in conjunction with the insulin dose and the body weight changes. We will analyse these two primary end points in a hierarchical order, where the difference in the change of HbA1c from baseline to week 12 between the study groups is analysed first (at a significance level of 0.05). If the null hypothesis of this primary outcome (i.e. there is no difference in the change of HbA1c from baseline to week 12 between the two study groups) is rejected, the second primary outcome (i.e. the difference in the number of participants achieving a combined end point encompassing a body weight reduction of at least 2%, an insulin dose reduction of at least 10% and an absolute HbA1c reduction of at least 3 mmol/mol [0.3%]) will be tested at a significance level of 0.05. As the analysis will be performed in hierarchical order, according to the European Medical Agency (EMA) guideline on multiplicity issues in clinical trials (section 5.1.2.) no reduction or splitting of the α level is required.^35^

For the primary analysis of the primary outcomes, we will perform an intention‐to‐treat (ITT) analysis of all participants randomized using an unpaired t‐test for the change in HbA1c (alpha = 5%), followed by a chi‐square test comparing the two proportions of the co‐primary outcome (alpha = 5%), if the first test rejects the null hypothesis.

We will then perform sensitivity analyses for the primary outcomes using multivariate imputation by chained equations) for missing data in the ITT cohort. Additional sensitivity analyses will be performed in the per protocol cohort (people adherent to the intervention according to section 2.8.19) without and with data imputation for missing data.

Furthermore, analysis of covariance or multiple linear regression model adjusting for baseline HbA1c and multiple logistic regression model adjusting for baseline co‐primary, respectively, will be performed using the ITT population.

Finally, we will perform linear mixed‐effect models without multiplicity adjustment and generalized linear mixed models, respectively, for the primary outcomes in the ITT population.

Continuous secondary outcomes will be analysed using both unpaired t‐test and linear mixed‐effect models.

Transformation will be considered if data are not normally distributed. For categorical data, summary tables will include frequencies and percentages. For continuous data, means, standard deviations, medians and upper and lower quartiles will be presented. Change in outcomes over time, overall and by treatment groups will be displayed in line plots/boxplots with corresponding global and pairwise p‐values. All analyses will be performed in R version 4.1.0.

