### Sample size estimation

2.3

Sample size was estimated using the parameters of a previously published randomized controlled trial^23^ that investigated the effects of intermittent fasting on glycaemic control in people with type 2 diabetes mellitus. We based our sample size estimation on the baseline HbA1c data of this study 66 ± 7 mmol/mol (8.2 ± 0.6%) and estimated that a sample size of 23 participants in each group will have a power of 85% to detect a clinically important mean difference of 6 ± 7 mmol/mol (0.5 ± 0.6%) in HbA1c between the groups at a two‐sided alpha error of 5%. For the co‐primary outcome a sample size of 20 participants in each group would provide a power of 0.80 to detect a difference in proportion of 40% between the intermittent fasting and the control group. This calculation assumes 10% of the control group will reach the co‐primary end point (combined end point encompassing a body weight reduction of at least 2%, an insulin dose reduction of at least 10% and an absolute HbA1c reduction of at least 3 mmol/mol [0.3%]).

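### The primary, gatekeeping HbA1c test is an unadjusted t-test on change, while the more precise baseline-adjusted ANCOVA already planned is only supporting

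*Protocol article*

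**What the plan says.** Section 2.8.19 (Statistical assessment) of the protocol article sets this order for HbA1c:

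- The primary analysis is an intention-to-treat "analysis of all participants randomized using an unpaired t‐test for the change in HbA1c", at the 5% level.
- The second primary outcome, the composite of weight, insulin dose and HbA1c, is tested only "if the first test rejects the null hypothesis".
- Sensitivity analyses with imputation and in the per-protocol cohort follow.
- After these comes "analysis of covariance or multiple linear regression model adjusting for baseline HbA1c", in the intention-to-treat population, and then mixed models.

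The article gives no reason for putting the unadjusted test first and no correlation between baseline and week-12 HbA1c. Section 2.3 (Sample size estimation) states that "a sample size of 23 participants in each group will have a power of 85" per cent for a difference of 6 with SD 7 mmol/mol. It takes the SD from baseline HbA1c values in an earlier trial. Section 2.8.23 (Study status) reports that all 46 participants have been recruited.

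**The concern.** A change score uses baseline HbA1c with a slope fixed at 1. ANCOVA estimates the slope. When the true slope is below 1, which is usual when baseline and follow-up vary to a similar degree, subtracting the whole baseline over-corrects. This adds noise, and part of any chance difference between the arms at baseline carries into the estimate through regression to the mean.

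Three features make this matter here. The HbA1c test is the gate, so a missed rejection also closes off the composite, which section 2.7.3 presents as essential to interpretation. Recruitment is closed, so more precision can come only from the analysis. And with 23 per arm, chance differences in mean baseline HbA1c are not negligible.

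**Working it through.** **Inputs.** From section 2.3: difference 6 mmol/mol, SD 7 mmol/mol (0.5 and 0.6 in percentage units), 23 per arm, two-sided 5%. Assumed, because the article gives neither: rho from 0.3 to 0.9, and equal variances at baseline and week 12 unless stated otherwise.

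**The plan's own figure.** The standard error of the difference is 7 × √(2/23) = 2.06, so the noncentrality is 6/2.06 = 2.91. The noncentral t with 44 degrees of freedom gives power 81.1% (82.8% by the normal approximation). With 0.5 and 0.6 it is 78.9%. The stated 85% is not reproduced from either pair. That is a separate matter; the comparison below starts from 81.1%.

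**Variance ratio.** With a common SD σ at both times, Var(change) = 2σ²(1 − rho) and the ANCOVA residual variance is σ²(1 − rho²). The ratio is (1 − rho²)/[2(1 − rho)] = (1 + rho)/2.

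**Reading A: 7 is the SD of change.** The ANCOVA SD is 7 × √((1 + rho)/2), with 43 degrees of freedom.

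| rho | variance ratio | t-test power | ANCOVA power | ANCOVA 95% CI half-width |
|---|---|---|---|---|
| 0.3 | 0.65 | 81.1% | 94.1% | 3.36 |
| 0.5 | 0.75 | 81.1% | 90.7% | 3.61 |
| 0.7 | 0.85 | 81.1% | 86.9% | 3.84 |
| 0.9 | 0.95 | 81.1% | 83.0% | 4.06 |

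The t-test half-width is 4.16 mmol/mol throughout. At rho 0.5 the t-test would need about 23/0.75 = 30.7, so 31 per arm, for the same precision. A simulation of 10,000 trials, which includes the cost of estimating the slope, gave 81.6% against 90.0% at rho 0.5 and 81.3% against 86.4% at rho 0.7.

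**Reading B: 7 is the cross-sectional SD**, as the source named in section 2.3 suggests. The SD of change is then 7 × √(2(1 − rho)) and the ANCOVA SD is 7 × √(1 − rho²).

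| rho | SD of change | t-test power | ANCOVA SD | ANCOVA power |
|---|---|---|---|---|
| 0.3 | 8.28 | 67.1% | 6.68 | 84.6% |
| 0.5 | 7.00 | 81.1% | 6.06 | 90.7% |
| 0.7 | 5.42 | 95.6% | 5.00 | 97.8% |

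**Chance imbalance, reading B.** The baseline mean difference has SD 7 × √(2/23) = 2.06 mmol/mol. A fraction (1 − rho) of an imbalance stays in the change-score estimate. At rho 0.5 a one-SD imbalance shifts it by 0.5 × 2.06 = 1.03, about one sixth of the target difference of 6. The two readings share this figure only at rho 0.5. If 7 is the SD of change, the baseline-difference SD is about 1.7 at rho 0.3 and 2.7 at rho 0.7.

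**Unequal variances.** Let the week-12 SD be 1.3 times the baseline SD, with rho 0.7 and baseline SD 1. Var(change) = 1 + 1.69 − 2 × 0.7 × 1.3 = 0.87. The ANCOVA residual variance is 1.69 × (1 − 0.49) = 0.862. The ratio is 0.99, because the slope is 0.7 × 1.3 = 0.91, already close to 1.

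**The case against.** The best defence is that nothing is wrong with the planned test as a test. It is pre-specified, matches an endpoint defined as change, is unbiased under randomization and holds its type I error. The adjusted analysis is planned too, so readers will see it. All of that stands and limits the point to efficiency. It does not justify the order: with baseline as covariate, modelling week-12 HbA1c or its change gives the same treatment estimate, so ANCOVA addresses the stated endpoint equally well. Nor does a supporting ANCOVA help at the gate, where only the t-test counts.

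The size of the gain is also open to challenge. It rests on an assumed rho and on equal variances, and it is about 2 percentage points at rho 0.9 under reading A and at rho 0.7 under reading B. This is correct, so no single figure should be quoted as the loss.

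Two stronger readings are tempting. A reader might infer that chance baseline imbalance passes straight into the result and biases it. It does not: the change score already subtracts baseline, only (1 − rho) of an imbalance remains, and that variation is already in the t-test's standard error. It is the same loss as the power deficit seen conditionally, not an additional one. A reader might also see a fault in the sentence "Continuous secondary outcomes will be analysed using both unpaired" t-tests and mixed models, with neither named as leading. The article makes no confirmatory claim for those outcomes, and the choice of lead model is commonly left to an analysis plan, which is not shown here.

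**Conclusion.** The point holds as an avoidable loss of precision in the test that gates both primary conclusions. It is not a validity error. With equal variances ANCOVA is ahead at every rho below 1 considered. Under reading A the gain in power runs from 13 percentage points (rho 0.3) to 2 (rho 0.9). Under reading B it runs from about 17 (rho 0.3) to about 2 (rho 0.7). If the week-12 SD is well above the baseline SD the gain can shrink to almost nothing, as the ratio of 0.99 shows. The direction is well supported. The size depends on rho, on the variance ratio and on what the 7 represents, none of which the article settles. The change is worth making because the baseline value is already collected and the model already planned.

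**What to change.** Make ANCOVA of week-12 HbA1c on treatment and baseline HbA1c, in the intention-to-treat population, the single primary test and the one that opens the gate to the composite. Keep the unpaired t-test on change as a sensitivity analysis.

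The statistical cost is one degree of freedom (43 instead of 44). The procedural cost is larger than a reordering suggests: the trial is open and recruitment is complete, so the change needs a dated amendment, documented before outcome data are analysed by arm. If results by arm have already been seen, the swap should be disclosed as post hoc.

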**FIGURE 1 dme14813-fig-0001:**
[figure not shown]
Flow chart of the intervention (an optional single follow‐up after 1 year will be added)

46 participants (23 per group) with insulin‐treated type 2 diabetes mellitus are randomly assigned to ‘intermittent fasting’ or ‘control group’, in a 1:1 ratio. Intermittent fasting comprises 3 days (Monday, Wednesday, Friday) of 75% caloric restriction (i.e. only 25% of the recommended calorie intake; this intake is only allowed as breakfast and/or lunch to maintain an 18 hours period of fasting) and 4 days (Tuesday, Thursday, Saturday and Sunday) of 0% caloric restriction (i.e. ad libitum calorie intake) in 1 week.

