#### Insulin adaptation

2.8.18

To prevent hypoglycaemia caused by intermittent fasting,^23^ a specific protocol for insulin dose adaptation is used, adapted from Unnikrishnan et al.^34^ 4 weeks prior to the initiation of dietary intervention, participants switch to the same insulin treatment, consisting of glargine U300 as basal insulin and a short‐acting insulin. Insulin U300 is administered in the morning. Participants using premixed insulin receive 70% of their daily insulin dose as glargine U300 whereas participants using basal‐bolus insulin treatment continue on their original basal insulin dose but are switched to glargine U300. Participants who are allocated to the control group continue glargine U300 and prandial insulin as started in the switch phase with dose adjustments when deemed necessary by the treating physician.

Participants in the intermittent fasting group continue the same treatment as during the switch phase on the eating days and reduce the basal insulin by 20% on the fasting days with no prandial insulin. In case the blood sugar falls below 3.9 mmol/L, the fast is broken, and the glargine U300 dose is reduced by another 10% (on fasting and eating days) for the remainder of the study. (Table 1) Within the insulin switch phase, we standardise the insulin regimen but aim to sustain glucose control from screening without significant intensification of glucose control. During the intervention phase on days with 0% calorie restriction, we aim for 5.6–7.2 mmol/L in the fasting state and <11.1 mmol/L2h postprandial (for detailed insulin dose adjustments, see Table 2). Participants already using glargine U300 are able to start the intervention 7 days ±1 after the screening visit if treatment is stable at the discretion of the treating physician.

**TABLE 1 dme14813-tbl-0001:** Insulin regimen

	Eating days	Fasting days
Control group	Continue insulin dose from switch phase	Not applicable
Intermittent fasting group	Use insulin dose from switch phase	20% basal insulin reduction, no prandial insulin

**TABLE 2 dme14813-tbl-0002:** Insulin dose adjustment on fasting days and eating days

Fasting days	
<3.9 mmol/L	Fast stopped and additional 10% reduction of glargine U300 dose (on fasting and eating days), intake of 24 g of carbohydrates
3.9–5.5 mmol/L	Regular monitoring of glucose level trend
5.6–7.2 mmol/L	Target range
7.3–13.9 mmol/L	Regular monitoring of glucose level trend

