#### Adherence to the protocol

2.8.20

Adherence to the protocol is assessed every 2 weeks with telephone calls and by discussing the food diary at the on‐site visits in all study participants. Furthermore, fasting periods can be assessed by the CGM. Adherence is defined as following the caloric restrictions (i.e. at maximum 25% of recommended calorie intake on a fasting day) on more than 75% of the fasting days.

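### The per-protocol cohort is defined by a rule that can exclude fasters but not controls, and its cross-reference points to the wrong section

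*Protocol article*

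**What the plan says.** Section 2.8.19 (Statistical assessment) makes the primary analysis intention-to-treat in everyone randomised. It then adds: "Additional sensitivity analyses will be performed in the per protocol cohort". The cohort is described only as "people adherent to the intervention according to section 2.8.19", and it is to be analysed both without and with imputation.

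The adherence rule is in the next section, 2.8.20: "Adherence is defined as following the caloric restrictions", with the threshold given as "at maximum 25% of recommended calorie intake on a fasting day) on more than 75% of the fasting days". The same section says how the information is gathered: "Adherence to the protocol is assessed every 2 weeks with telephone calls and by discussing the food diary". This applies to all study participants, but no criterion is given for a control.

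The text under Figure 1 schedules fasting days for one arm only: "Intermittent fasting comprises 3 days (Monday, Wednesday, Friday) of 75% caloric restriction". Table 1 in section 2.8.18 enters "Not applicable" for controls in its fasting-days column.

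**The concern.** A per-protocol analysis supports a randomised result only if membership of the cohort is decided in the same way in both arms. Here the only stated rule is a behaviour asked of one arm after randomisation. Fasters who miss the threshold leave, while controls have nothing to miss and stay. If keeping to the diet is related to HbA1c change, for whatever reason, the two groups would differ even if fasting had no effect.

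What is at stake is how the supporting analyses are read. They are labelled sensitivity analyses of both primary outcomes, so agreement with the intention-to-treat result would be taken as reassurance and disagreement as a warning. A comparison of selected fasters with unselected controls answers a different question and can properly serve as neither.

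**Working it through.** **The text, step by step**

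1. Section 2.8.19 refers to 2.8.19 for adherence. That section contains no adherence rule, so the reference is wrong. The only rule in the document is in 2.8.20.
2. In the fasting arm there are 3 fasting days a week for 12 weeks, 3 × 12 = 36. More than 75% means more than 0.75 × 36 = 27, so at least 28 days must qualify. A faster with 27 or fewer is out.
3. In the control arm there are 0 fasting days, so the proportion is 0/0 and the rule cannot be evaluated. Either no control qualifies and there is no comparison, or all controls stay and only the fasting arm is filtered. Only the second can be analysed.
4. Imputation fills in missing outcomes for people inside the cohort. It does not bring back fasters excluded for non-adherence, so both versions carry the same selection.

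**Illustration of size**

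The plan gives no figure to reproduce here. Inputs from section 2.3: 23 per arm, SD 7 mmol/mol and target difference 6 mmol/mol. Using 7 as the SD of HbA1c change is an assumption. So are the share of fasters who adhere (p) and the correlation (r) between adherence tendency and HbA1c change; the document gives neither.

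Under a bivariate normal model with no effect of fasting, keeping the most adherent fraction p of one arm shifts that arm's mean by

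shift = 7 × r × φ(c)/p, with c = z(1 − p).

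| p | Fasters kept (23 × p) | φ(c)/p | r = 0 | r = 0.2 | r = 0.3 | r = 0.5 |
|---|---|---|---|---|---|---|
| 0.80 | 18.4 | 0.350 | 0 | 0.49 | 0.73 | 1.22 |
| 0.70 | 16.1 | 0.497 | 0 | 0.70 | 1.04 | 1.74 |
| 0.60 | 13.8 | 0.644 | 0 | 0.90 | 1.35 | 2.25 |

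Entries under r are absolute shifts in mmol/mol. For example, 7 × 0.5 × 0.644 = 2.25, which is 2.25/6 = 37.5% of the target difference. If better adherers have larger HbA1c falls, the shift favours fasting. If they have smaller falls, the shift has the same size and works against fasting.

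A simulation (40,000 trials per cell, no true effect, 23 controls all kept, unpaired t-test) reproduced these shifts. The two-sided 5% test rejected in about 5% of trials at r = 0. At r = 0.3 and r = 0.5 it rejected in 6.2% and 8.3% for p = 0.80, and in 8.5% and 14.8% for p = 0.60.

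**Direction**

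Section 2.8.18 has the fast broken when glucose falls below 3.9 mmol/L. Section 2.8.20 does not say whether such a day counts as adherent. If it does not, the rule may remove fasters with the lowest glucose, which would work against fasting. If motivated participants both adhere and improve more, the rule works in favour of fasting. The document does not settle which dominates.

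**The case against.** The strongest reply is that no primary conclusion rests on this cohort. The main test, the hierarchy, the covariate-adjusted models and the mixed models all use the intention-to-treat population, as does the first imputation analysis. That stands, and it limits the weight of the point.

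A second reply is that detailed membership rules commonly sit in a full protocol or analysis plan that is not shown, and that adherence information is collected in both arms. Criteria for controls may therefore exist elsewhere. This stands in part. But the article does not leave the cohort open: it states a definition, points it at the wrong section, and the only rule it can mean is one-sided.

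A third reply is that leaving all controls in is the familiar form of a per-protocol analysis against usual care. That is the natural reading, and on it the comparison is still not randomised, although it is offered as a sensitivity analysis.

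A reader might go further and infer that the cohort is built to favour fasting. The documents do not support this, because the direction depends on why people fail the rule and on how stopped fasts are counted. Nor do they support treating the shifts above as an estimate: at r = 0 there is no bias at all, and negative values of r reverse it.

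A reader might also conclude that a complier-average causal effect should replace the cohort. That estimator assumes assignment acts on the outcome only through meeting the threshold. A faster who complies on 70% of days counts as unexposed yet may well be affected, and assignment itself changes the insulin regimen (Table 1). The estimate is roughly the intention-to-treat effect divided by the adherent share, so at 60% it multiplies that effect by 1/0.6 = 1.67. If the assumption fails, that inflates the result.

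**Conclusion.** The point holds for the per-protocol sensitivity analyses of both primary outcomes, with and without imputation, and for nothing else in the plan. The cross-reference is wrong, and the rule it must mean selects on post-randomisation behaviour in one arm only. Under the stated assumptions (SD of change 7, 60–80% adherent, correlation 0 to 0.5 in size) the HbA1c difference could be displaced by 0 to about 2.3 mmol/mol in either direction. No corresponding figure was worked out for the composite outcome. The defect is worth correcting because the remedy is cheap and the label invites over-reading, but it does not threaten the intention-to-treat result.

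**What to change.** - Correct the reference in section 2.8.19 to 2.8.20.
- Define the per-protocol cohort by criteria that both arms can meet or fail, for example a week-12 visit in window and no major eligibility violation.
- If an analysis restricted to adherent fasters is kept, report it as non-randomised and descriptive, not as a sensitivity check of the randomised comparison.
- State how a fasting day stopped under the glucose rule in section 2.8.18 counts towards the 75% threshold. This concerns the analysis definition only, not the clinical rule.
- Optionally, add a complier-average estimate as exploratory, with its exclusion-restriction assumption and the reasons to doubt it stated alongside.

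The cost is a few sentences of analysis wording. No new data are needed, and completed recruitment is no obstacle, though the wording should be fixed before outcomes are compared by arm. The downside is that the per-protocol result will carry less weight as support for efficacy among those who adhere.

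### Continuous secondary outcomes get two unranked analyses, a t-test and a mixed model, and the plan does not say which gives the reported result (minor)

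*Protocol article*

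**What the plan says.** Section 2.8.19 (Statistical assessment) gives one sentence on the tests for these outcomes: "Continuous secondary outcomes will be analysed using both unpaired t‐test and linear mixed‐effect models". The two methods stand side by side. Neither is called the main one, and no rule covers a disagreement. The model's fixed effects, its handling of baseline and the contrast to be tested are not stated. The closing text of the section promises plots of change over time "with corresponding global and pairwise p‐values", without saying which method supplies those p-values.

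The primary outcomes are treated differently. There the section opens with a single choice: "For the primary analysis of the primary outcomes, we will perform an intention‐to‐treat (ITT) analysis of all participants randomized using an unpaired t‐test", followed by a chi-square test for the second primary outcome. The imputation and per-protocol analyses are then labelled as sensitivity analyses. Covariate-adjusted models follow, and mixed models come last: "Finally, we will perform linear mixed‐effect models without multiplicity adjustment and generalized linear mixed models, respectively, for the primary outcomes in the ITT population". The last two groups carry no sensitivity label, but a primary analysis has been named before them.

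Section 2.7.2 fixes the visit for each change outcome. It is 12 weeks throughout, except that insulin dose is also listed at 4 and 8 weeks.

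**The concern.** An unpaired t-test on change and a linear mixed model need not give the same answer, even for the same outcome at the same visit. The t-test uses participants measured at both visits and subtracts baseline in full. A mixed model can keep participants with a missing visit, can borrow information from other visits and, depending on its form, can adjust for baseline by regression.

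Followed as written, the plan produces two p-values per continuous secondary outcome and leaves open which one the abstract or the discussion will rest on. If that choice is made after the results are known, the error rate per outcome is no longer 5%. Where there is a real effect, readers may meet one significant and one non-significant answer to the same question, with nothing in the plan to settle it.

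**Working it through.** The plan states no figure on this point, so there is none to reproduce. The check asks how far the two analyses can diverge.

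**Inputs from the protocol article**
- Group size: "46 participants (23 per group) with insulin‐treated type 2 diabetes mellitus are randomly assigned" (text with Figure 1), so n = 23.
- Level: "at a two‐sided alpha error of 5" per cent in section 2.3, stated for the first primary outcome. No level is given for secondary outcomes, so 5% two-sided is assumed.

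**Assumptions**
- Correlation ρ between baseline and the visit of interest: 0.3 to 0.9.
- Equal SD at both visits (set to 1) and complete data.
- The mixed model is represented by a baseline-adjusted comparison at the same visit (ANCOVA).
- True effect for the power figures: 0.6 SD.

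**Formulas**
- t-test on change: variance of the group difference = 2(1 − ρ) × 2/n.
- Baseline-adjusted difference: variance ≈ (1 − ρ²) × 2/n.
- Correlation of the two test statistics = √((1 + ρ)/2).
- Chance that at least one is significant = 1 − P(|Z1| < 1.96 and |Z2| < 1.96), for bivariate normal Z with that correlation.
- Chance that the verdicts differ = 2 × P(at least one significant) − power 1 − power 2.

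**Worked case, ρ = 0.5**
- Correlation of the statistics = √(1.5/2) = 0.866.
- No effect: at least one significant in 7.3% of trials.
- Standard errors: √(1.00 × 2/23) = 0.295 for change and √(0.75 × 2/23) = 0.255 adjusted.
- Effect 0.6 SD: 0.6/0.295 = 2.03 and 0.6/0.255 = 2.35. The normal approximation gives power 0.53 and 0.65, with at least one significant in 0.686.
- Verdicts differ: 2 × 0.686 − 0.530 − 0.652 = 0.190.

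**Range** (simulation with t reference distributions, 100,000 trials per row)

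| ρ | Either p < 0.05, no effect: normal formula | Same, simulated | Power at 0.6 SD: t-test on change | Power: adjusted | Verdicts differ at 0.6 SD |
|---|---|---|---|---|---|
| 0.3 | 7.77% | 7.75% | 0.39 | 0.54 | 24% |
| 0.5 | 7.34% | 7.19% | 0.51 | 0.62 | 19% |
| 0.7 | 6.81% | 6.81% | 0.73 | 0.79 | 11% |
| 0.9 | 6.04% | 6.08% | 0.99 | 0.99 | 0.4% |

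Each analysis alone holds 4.9% to 5.1%. Repeated simulations gave 6.0% to 6.2% at ρ = 0.9 and 7.6% to 7.8% at ρ = 0.3, so about 6.0% to 7.7% is a fair summary. At ρ = 0.5 and 0.6 SD, power was 0.51 to 0.52 for change and 0.62 to 0.63 adjusted.

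**When the two coincide.** A random-intercept group-by-time model without baseline adjustment was fitted to simulated two-visit data with nothing missing. Its interaction statistic equalled the t-test statistic on change (for example 1.896 in both). With 4 of 46 week-12 values missing, the statistics separated (for example 0.389 against 0.468). With several follow-up visits, such a model also pools residual variance across visits, so its standard error at week 12 need not match that of the t-test.

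**The case against.** **Much of the list may not be affected.** The Methods paragraph of the abstract places resting metabolic rate, glucose tolerance, body composition by DXA and stool sampling at the start and the end of the intervention. For two visits, complete data and a plain group-by-time model, the two analyses are the same test. This stands, and it rules out saying that every continuous secondary outcome is affected.

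**Baseline adjustment is not documented for the mixed model.** For the primary outcomes, section 2.8.19 lists baseline-adjusted regression and mixed models separately. The 6.0% to 7.7% range therefore rests on an assumption about an undescribed model. This also stands.

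**Larger figures can be produced, but they answer another question.** Comparing the week-12 t-test with a baseline-adjusted average over three follow-up visits gives about 8.4% and, at 0.6 SD, 39% disagreement (ρ = 0.5). Section 2.7.2 defines no average-over-visits outcome, so these figures should not be used against the plan.

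**Choosing the favourable result is not announced.** A reader might infer that the plan intends this. It does not say so. It commits to running both methods, and if both are reported any disagreement is visible. The plan only leaves the choice open.

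**Nothing confirmatory depends on it.** The hierarchical test covers the two primary outcomes only. Section 2.7.2 lists 14 change outcomes, and testing all at 5% would already give 1 − 0.95^14 = 51% familywise error if they were independent. Ranking two methods does not make these p-values confirmatory. This stands and lowers the weight.

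**An analysis plan that is not shown might rank them.** It might. But the article does more than stay silent: it prescribes two tests jointly, in a section that does name one primary analysis for the primary outcomes. That wording is what needs changing.

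**Conclusion.** The point holds as a minor one. The article prescribes two analyses of equal standing for each continuous secondary outcome and does not say which gives the reported result.

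If the mixed model adjusts for baseline and either significant result could be headlined, the false-positive rate per outcome is about 6.0% to 7.7% instead of 5% (23 per group, complete data, ρ from 0.9 down to 0.3). At an assumed 0.6 SD effect and ρ = 0.5, the verdicts differ in about 19% of trials. The correlation, the effect size and the form of the model are all assumptions.

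The issue matters most for insulin dose at 4, 8 and 12 weeks, for outcomes with missing values, and wherever baseline is adjusted for. A reader might infer that the main findings are at risk. They are not, because the primary outcomes have a named primary analysis and a fixed testing order.

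**What to change.** Replace the sentence in section 2.8.19 with wording such as:

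> For each continuous secondary outcome, the reported result is the between-group difference with 95% confidence interval at the visit named in section 2.7.2, from one linear model adjusted for the baseline value. Where there are several follow-up visits, this is a linear mixed model with baseline value, group, visit and group-by-visit. Where there is one, it reduces to analysis of covariance. The unpaired t-test on change is reported as a sensitivity analysis.

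The p-values shown with the plots should be tied to the same model. The ranking should be recorded before the results are seen, since section 2.8.23 reports recruitment as complete.

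The change costs a few lines and no new data. Both types of analysis are already planned. It also gains power: about 0.63 against 0.52 at 0.6 SD and ρ = 0.5. The downside is small: the t-test is no longer the headline for these outcomes, and their main analysis differs in form from the primary t-test. If the authors prefer to keep the two aligned, naming the t-test as the reported result would also remove the ambiguity, at the price of that power.
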